#### Participants

2.2.2

The target population includes the general population that meets the following inclusion criteria:

Aged ≥ 60 years;Community-dwelling residents for at least 1 year;Ability to communicate with the researchers and express themselves;Provided written informed consent.

The exclusion criteria are as follows:

Older adults with cognitive impairment or major mental disorder;Palliative care (life expectancy <6 months);Permanently bedridden.

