### Study questions

1.3

This study hypothesises that older adults have physiological, psychological, and social participation and environmental and information needs in CBR. Since older adults have multiple needs at the same time, there may be several fixed combinations of these needs in the older adults population (e.g., “Physiological-psychological” combination, “socially-participation-environment” combination). Each older adults person will fall into one of these categories, and contextual characteristics, individual characteristics, health behaviours, and health outcomes influence these combinations.

We aim to address the following three research questions: (i) When older adults individuals have multiple rehabilitation needs, is it more likely that these needs will be combined in a specific manner rather than randomly? (ii) Do older adults with similar characteristics have similar needs? (iii) What key factors are associated with the needs of older adults with multiple CBR needs?

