	Defecation functions	b525 Defecation functions b620 Urination functions
	Weight maintenance functions	b530 Weight maintenance functions
	Functions of the joints and bones	b710 Mobility of joint functions b715 Stability of joint functions b720 Mobility of bone functions
	Muscle functions	b730 Muscle power functions b735 Muscle tone functions b740 Muscle endurance functions
	Movement functions	b750 Motor reflex functions b755 Involuntary movement reaction functions b760 Control of voluntary movement functions b765 Involuntary movement functions b770 Gait pattern functions
Mental functions	Cognitive function	b110 Consciousness functions b114 Orientation functions b140 Attention functions b144 Memory functions b164 Higher-level cognitive functions
	Sleep functions	b134 Sleep functions
	Psychomotor functions	b147 Psychomotor functions
	Emotional functions	b152 Emotional functions
Individual activities	Changing and maintaining body position	a410 Changing basic body position a415 Maintaining a body position a420 Transferring oneself
	Carrying, moving, and handling objects	a430 Lifting and carrying objects a435 Moving objects with lower extremities a440 Fine hand use a445 Hand and arm use
	Walking and moving	a450 Walking a455 Moving around a460 Moving around in different locations
	Self-care	a510 Washing oneself a520 Caring for body parts a530 Toileting a540 Dressing a550 Eating a560 Drinking a570 Looking after one’s health
Social participation	Interpersonal interactions	p710 Basic interpersonal interactions p720 Complex interpersonal interactions
	Interpersonal relationships	p730 Relating with strangers p740 Formal relationships p750 Informal social relationships p760 Family relationships p770 Intimate relationships
	Community life participation	p910 Community life
	Recreation and leisure	p920 Recreation and leisure
Environment	Use of assistive devices	e115 Products and technology for personal use in daily living e120 Products and technology for personal indoor and outdoor mobility and transportation e125 Products and technology for communication
	Cultural and entertainment	e140 Products and technology for culture, recreation, and sport
	Barrier-free environment transformation	e150 Design, construction and building products, and technology of buildings for public use e155 Design, construction and building products, and technology of buildings for private use

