#### Data collection

2.2.3

Specially trained researchers will work closely with community workers to collect data from the community. First, the researchers will determine the eligible participants according to the inclusion and exclusion criteria through the community health records. The community staff will then contact eligible participants and agree on the investigation time and location based on their initial consent. The place to conduct an investigation is usually the community office or participants’ homes. Subsequently, the two researchers will meet with the participants at an agreed time and place. The researchers will talk to the older adults or their caregivers to explain the purpose of the study and the concept of CBR. Their power includes privacy protection and the termination of investigations at any time. Individuals willing to participate will provide written informed consent before completing the survey. Finally, one of the researchers will send an e-questionnaire QR code prepared in advance to qualified participants. The questionnaire will be completed after the code is scanned using a smartphone. Our researchers will help older people who have difficulty using smartphones complete and submit the questionnaire. After completing the questionnaire, we will pay the participants a particular reward or an equivalent gift (approximately $4–5). Data will be extracted using a questionnaire platform and sorted into Microsoft Excel. The instruments used are as follows:

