#### Interpretation of the results

2.4.4

Once the LCA model is determined, each participant will be assigned to one of the need pattern categories with the highest probability. Through LCA, we will answer our study questions (i) and (ii) and provide a scientific explanation to identify the multiplicity and latent class of rehabilitation needs of older adults in the community and the distribution proportion of each category.

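### Class shares are described for older adults in the community without restriction, but the exclusions, which overlap with domains the questionnaire classifies, confine them to eligible people, and the limitations do not say so

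*Protocol article*

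**What the plan says.** Participants (2.2.2) opens: "The target population includes the general population that meets the following inclusion criteria". The inclusion criteria are age 60 or over, at least a year's residence in the community, "Ability to communicate with the researchers and express themselves", and written consent. A separate exclusion list follows: "Older adults with cognitive impairment or major mental disorder", palliative care, and "Permanently bedridden". Section 2.3.2 applies the same criteria to the main study.

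The scope of the results is put more widely. Study questions (1.3) says: "Each older adults person will fall into one of these categories". Interpretation of the results (2.4.4) says that the analysis will "identify the multiplicity and latent class of rehabilitation needs of older adults in the community and the distribution proportion of each category".

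Table 1, the item pool for the questionnaire, lists under cognitive function "b110 Consciousness functions b114 Orientation functions b140 Attention functions b144 Memory functions b164 Higher-level cognitive functions". It also lists emotional functions, changing position and transferring, and self-care.

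The limitations in the Discussion cover the region and the subjectivity of questionnaire answers. They do not mention the exclusions. Data collection (2.2.3) says that researchers will "determine the eligible participants according to the inclusion and exclusion criteria through the community health records".

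**The concern.** An exclusion unrelated to what is being classified would do little to class shares. These exclusions are related to it. Cognitive impairment is removed at entry, yet cognitive function is one of the needs to be sorted into classes. The same holds in part for emotional functions (major mental disorder) and for transfer and self-care (permanent bed confinement).

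A share estimated in the eligible sample is thus a share of eligible people. Read as 2.4.4 is worded, it would be taken as a share of older people in the community, and the article intends the results to guide rehabilitation policy and services. A larger sample does not remove this kind of error, because it comes from who can enter and not from sampling variation.

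**Working it through.** **1. Do the passages agree on the population?**

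| Place | Population named |
|---|---|
| 2.2.2, opening | People meeting the inclusion criteria |
| 2.2.2 and 2.3.2, as applied | Those people, less the three exclusion groups |
| 1.3 | Each older person |
| 2.4.4 | Older adults in the community |
| Discussion, limitations | Region and self-report only |

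A bedridden person who can talk, or a person with cognitive impairment who can still communicate, meets the inclusion criteria and is then excluded. The sample is therefore narrower than the target population in 2.2.2, and narrower again than the wording of 2.4.4.

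**2. What could the gap be?** The only relevant stated figure is the sample size: 50 clusters × 80 = 4,000, which reproduces. The documents give no excluded share and no need profile for excluded people, so the rest is illustration. Let

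- s = share of a class among eligible people (assumed 15%)
- e = share of the full population that is excluded (assumed 2% to 20%)
- h = share of excluded people who belong to that class (unknown, 0 to 100%)

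Share in the full population = s(1−e) + e·h. The shift from s is e(h−s). With h = 0 and h = 1 the bounds are s(1−e) and s(1−e)+e.

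| e | Lower bound | Upper bound | Shift if h = 15% | Shift if h = 60% |
|---|---|---|---|---|
| 2% | 0.15×0.98 = 14.7% | 16.7% | 0 | 0.02×0.45 = +0.9 points |
| 5% | 0.15×0.95 = 14.25% | 19.25% | 0 | 0.05×0.45 = +2.25 points |
| 10% | 0.15×0.90 = 13.5% | 23.5% | 0 | 0.10×0.45 = +4.5 points |
| 20% | 0.15×0.80 = 12.0% | 32.0% | 0 | 0.20×0.45 = +9.0 points |

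Every interval contains 15%. Arithmetic alone does not fix the direction; h > s is needed for the eligible share to be too low.

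**3. Against sampling error.** SE = √[0.15×0.85/4000 × (1 + 79×ICC)], where 79 is the cluster size less one.

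- ICC 0: 0.56 points
- ICC 0.02 (assumed): 0.91 points
- ICC 0.05 (assumed): 1.26 points

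At e = 2% and h = 60% the shift is about one SE. At e = 10% and h = 60% it is 4.5/1.26 = 3.6 to 4.5/0.56 = 8.0 SEs. At h = 15% it is zero at any e.

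**4. If excluded people form a class of their own.** Then h = 0 for every estimated class, each estimated share falls to s(1−e), and the unseen class has share e. The bounds still hold, provided the class definitions stay as fitted in the eligible sample.

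**The case against.** The best defence is that 2.2.2 already restricts the target population and that 2.4.4 should be read with it. Part of this stands. People who cannot communicate fail an inclusion criterion and are outside the target from the start. The sentence in 1.3 is a hypothesis about class membership, none of the three research questions asks for a population share, and using the population aged 60 or over as the size measure in Sampling (2.3.3) allocates clusters without defining the population of inference. But 2.2.2 sets its target by the inclusion criteria and lists the exclusions apart, and 2.4.4 carries no restriction.

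Excluding people who cannot answer for themselves is usual in a questionnaire survey, and that is not contested here. A tally of exclusions is also a detail that an article may leave to its full protocol, so its absence is no defect. The point rests on statements in the article that do not agree.

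Three stronger readings are tempting, and the documents do not support them.

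- **Shares of high-need classes are too low.** A reader might infer this as fact. It is the plausible direction, but neither e nor h is given, and the bounds fall on both sides of the eligible share.
- **Heavy dependency cannot be observed.** Only the permanently bedridden are excluded on function. The ADL scale still records scores of 22 or more, Table 3 has a self-care disability category and a frailty covariate, and interviews may take place at home. Emotional and sleep needs can also occur without a major mental disorder. Table 1 is a first item pool, still to be filtered. Cognition is the clear case.
- **The excluded group is large because Background (1.1) puts depressive disorders at 36.8%.** Nothing links that figure to the exclusion for major mental disorder.

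**Conclusion.** The point holds as a mismatch between eligibility and the stated scope of the results. The planned class shares describe community-dwelling people aged 60 or over who meet the inclusion criteria and none of the exclusions. Shares of classes marked by cognitive or very high dependency needs are likely, but not shown, to be lower than in the whole community population.

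The documents do not allow the size to be calculated. Under the assumptions above it runs from nothing to several standard errors, and the upper bounds require every excluded person to fall into one class. This is a worthwhile, inexpensive correction to what the study may conclude. It is not a fault in whom the study enrols.

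**What to change.** 1. In 1.3 and 2.4.4, state that class shares refer to community-dwelling adults aged 60 or over who meet the inclusion criteria in 2.2.2 and none of its exclusions.
2. During the health-record screening in 2.2.3, count the people screened and those excluded, by reason and cluster. Count inability to communicate separately, since it is a failed inclusion criterion. Set this up before screening starts, because it may be hard to reconstruct later.
3. Report e, with s(1−e) to s(1−e)+e beside each class share, labelled as illustrative. Note that e depends on how complete the records are. The article does not say that every older resident is screened or that records capture cognitive impairment reliably, so the tallied e may be too low.
4. Add the exclusions to the limitations, and say that need for cognitive-function rehabilitation is measured only in people without cognitive impairment.

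The cost is a small tally during work already planned, one table and a few sentences. The downside is a narrower claim. Eligibility, sample size and the latent class analysis are unchanged.

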#### Data collection

2.2.3

Specially trained researchers will work closely with community workers to collect data from the community. First, the researchers will determine the eligible participants according to the inclusion and exclusion criteria through the community health records. The community staff will then contact eligible participants and agree on the investigation time and location based on their initial consent. The place to conduct an investigation is usually the community office or participants’ homes. Subsequently, the two researchers will meet with the participants at an agreed time and place. The researchers will talk to the older adults or their caregivers to explain the purpose of the study and the concept of CBR. Their power includes privacy protection and the termination of investigations at any time. Individuals willing to participate will provide written informed consent before completing the survey. Finally, one of the researchers will send an e-questionnaire QR code prepared in advance to qualified participants. The questionnaire will be completed after the code is scanned using a smartphone. Our researchers will help older people who have difficulty using smartphones complete and submit the questionnaire. After completing the questionnaire, we will pay the participants a particular reward or an equivalent gift (approximately $4–5). Data will be extracted using a questionnaire platform and sorted into Microsoft Excel. The instruments used are as follows:

##### Sociodemographic characteristics

2.2.3.1

Demographic characteristics will be measured using a personal information table developed by the researchers, including age, nationality, education, weight, height, marital status, residence, children, income, whether they have chronic diseases, and the type and number of chronic diseases.

##### Older adults’ CBRN-Q

2.2.3.2

The questionnaire developed by the researcher in the first phase mainly included body function needs, mental function needs, individual activities, social participation, environmental needs, and information needs.

##### Activities of daily living scale

2.2.3.3

The ADL scale measures the self-care abilities of older adults. It includes the physical self-maintenance (PSMS) and instrumental ADL (IADL) scales, comprising 14 items. The PSMS has six items for ADL—such as going to the toilet, eating, dressing, and grooming—while the IADL has eight items for using tools, such as making phone calls, shopping, doing housework, and taking medicine. Each item is rated on a scale of 1–4, with 1 being completely able to do it yourself and 4 being completely unable to do it yourself. The total score ranges from 14 to 56 points, with 14 indicating the complete self-care ability, 15–21 indicating decreased self-care ability, and ≥ 22 showing worse self-care ability in daily life. Higher scores indicate worse self-care ability. Cronbach’s alpha value is 0.884 (42).

##### Tilburg frailty indicator (TFI)

2.2.3.4

Compiled by Dutch scholars Gobbens et al. (43), TFI is mainly used to assess the frailty status of older adults. Chinese scholars Xing et al. (44) conducted cultural debugging and translation of the original scale, resulting in a new version of the TFI, including three dimensions of physical frailty (eight items), psychological frailty (four items), and social frailty (three items), with a total of 15 items. The symptoms mentioned in the presence of items are scored 1 point, while those not present are scored 0 points. The total score is 15 points, and TFI ≥5 points are judged as frailty. Cronbach’s alpha value is 0.686 (44).

#### Data analysis

2.2.4

This phase aims to test the reliability and validity of the older adults’ CBRN-Q in older adults. Moreover, we will retest the reliability of the ADL and FEI in the population we use. Data will be analysed using SPSS (version 29) and R software.

##### Reliability analysis

2.2.4.1

In the reliability analysis, we will mainly test Cronbach’s alpha values to test the internal consistency of CBRN-Q and the sub-questionnaire we developed. At the same time, we will re-examine the ADL and FEI scales in the older adults population. It is considered acceptable with a threshold of Cronbach’s α ≥ 0.70 (45).

##### Validity analysis

2.2.4.2

Exploratory factor analysis (EFA) and confirmatory factor analysis (CFA) will be used to assess the construct validity of the CBRN-Q. The collected samples will be randomly categorised into two independent subsets for EFA and CFA.

Before performing the EFA, we will test whether the data can be factor-analysed using Bartlett’s sphericity test and the Kaiser–Meyer–Olkin (KMO) test. The probability of Bartlett’s Test of Sphericity <0.05 or KMO >0.7 indicates that EFA can be performed (46). We will perform EFA using principal component analysis, oblimin rotation, and parallel analysis. We will keep entries with an item factor load >0.4 and no more than one factor (47, 48).

CFA will verify the factor structure of the CBRN-Q based on maximum likelihood estimates. CFA will use three indexes: comparative fit index (CFI), root-mean-square residual (SRMR), and root-mean mean-square error of approximation. CFI value ≥0.90 indicates an acceptable model fit, and ≤ 0.08 indicates a good fit; similarly, SRMR value ≤0.08 indicates a good fit (46).

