#### Study sample and sample size

2.2.1

Using purposive sampling, we will conduct a questionnaire survey on older adults in Zunyi, Guizhou Province. The sample size for questionnaire verification should be 10 times the number of questionnaire items (41). Because the questionnaire we developed is estimated to have 40–45 items, we will need at least 450 participants. Considering a 10% loss to follow-up rate, we determine that the sample size of the pre-trial is 500 participants.

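### Two validation thresholds are wrong as written: joining Bartlett and KMO by *or* disables the KMO limit, and the 0.08 limit is attached to CFI while RMSEA has none

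*Protocol article*

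**What the plan says.** All the rules stand in the protocol article, section 2.2.4.2 (Validity analysis).

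- **Starting the EFA.** For Bartlett's test and the Kaiser–Meyer–Olkin (KMO) measure: "Test of Sphericity <0.05 or KMO >0.7 indicates that EFA can be performed". Either condition is enough.
- **Fit of the confirmatory factor analysis (CFA).** Three indexes are announced: CFI, then "root-mean-square residual (SRMR), and root-mean mean-square error of approximation". The cut-offs follow. The first statement is "CFI value ≥0.90 indicates an acceptable model fit, and ≤ 0.08 indicates a good fit". The second, for the residual index, is "similarly, SRMR value ≤0.08 indicates a good fit". RMSEA does not appear again by name.
- **Extraction and retention.** The method is given as "We will perform EFA using principal component analysis, oblimin rotation, and parallel analysis". The rule for retaining an item is then "We will keep entries with an item factor load >0.4 and no more than one factor".

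The size comes from section 2.2.1: "The sample size for questionnaire verification should be 10 times the number of questionnaire items", and "Because the questionnaire we developed is estimated to have 40–45 items, we will need at least 450 participants". This is raised to 500 for 10% loss. The sample is then divided at random between EFA and CFA; the ratio is not given.

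**The concern.** A suitability check exists to stop a factor analysis of items that share too little. Bartlett's test asks only whether the correlation matrix differs from the identity. With 40–45 items and a few hundred people it detects very small correlations. KMO asks whether the correlations are large relative to the partial correlations, and it is the condition that could stop a poor item set. Joined by *or*, it cannot.

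The fit rule has a different fault: read literally it contradicts itself, and one of the three declared criteria has no limit. These rules decide whether the questionnaire is factor-analysed and whether its structure is called well-fitting, so they should be usable as printed before the pilot data are seen.

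**Working it through.** **1. The plan's own figure.** 45 items × 10 = 450; 450 / 0.90 = 500. The pilot size reproduces. With a 1:1 split (an assumption), each half has 450/2 = 225 to 500/2 = 250 people.

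**2. Bartlett by hand**, p = 45 items, n = 225, common correlation ρ = 0.05.

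- Statistic: −[(n − 1) − (2p + 5)/6] × ln|R|, on p(p − 1)/2 = 990 degrees of freedom.
- Multiplier: 224 − 95/6 = 208.2.
- For equal correlations, |R| = (1 − ρ)^(p−1) × (1 + (p − 1)ρ), so ln|R| = 44 × ln 0.95 + ln 3.2 = −2.257 + 1.163 = −1.094.
- Contribution of the true correlation: 208.2 × 1.094 ≈ 228. Expected statistic ≈ 990 + 228 = 1,218.
- The 5% critical value is about 990 + 1.645 × √1,980 + 1 ≈ 1,064.

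The expected statistic is far beyond the critical value.

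**3. KMO by hand, same setting.** KMO = Σr² / (Σr² + Σq²), where q are the partial correlations.

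- Mean r² ≈ ρ² + 1/224 = 0.0025 + 0.0045 = 0.0070.
- True partial correlation: 0.05 / (1 + 43 × 0.05) = 0.0159. Mean q² ≈ 0.0159² + 1/181 = 0.0003 + 0.0055 = 0.0058.
- KMO ≈ 0.0070 / 0.0128 ≈ 0.55, well under 0.7.

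So in this setting Bartlett passes and KMO fails.

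**4. Simulation of the rule.** Multivariate normal items, 40 or 45 items, n = 225 or 250, common correlation ρ, 600 samples per cell. Ranges run over the four combinations of items and n.

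| Average correlation | Pass with *or* | Pass with *and* |
|---|---|---|
| 0 | 5–7% | 0% |
| 0.02 | 31–40% | 0% |
| 0.03 | 66–80% | 0% |
| 0.05 | 99–100% | 0% |
| 0.08 | 100% | 5–13% |
| 0.10 | 100% | 55–81% |
| 0.15 or more | 100% | 100% |

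In every cell the *or* rule gave the same answer as Bartlett alone, so the KMO limit never changed a decision.

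Two other structures with 45 items:

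- n = 250, three item pairs correlated at 0.5, all other items independent: *or* passes 99.5%. Mean KMO is 0.46 and KMO never exceeds 0.7.
- n = 225–250, six domains, correlation 0.25 within a domain and 0 to 0.05 between: *or* passes 100%, *and* 1–64%. With 0.10 between domains both pass about 100%.

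**5. The fit sentence.** The only subject of the first clause pair is CFI. Taken literally, CFI ≥ 0.90 is acceptable and CFI ≤ 0.08 is good. No value meets both, and a model with CFI = 0.95 would be acceptable but never good. Matching indexes to limits:

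| Index named | Limit attached by name |
|---|---|
| CFI | ≥ 0.90, and ≤ 0.08 |
| SRMR | ≤ 0.08 |
| RMSEA | none |

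One limit is surplus and one index has none. The clause introducing the SRMR limit as a similar case also implies that the limit just before it was for another index where smaller is better. The likely explanation is that the word RMSEA was dropped before the first 0.08. No arithmetic is needed.

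**The case against.** **A coherent questionnaire is unaffected.** This stands. From an average correlation of 0.15 the two versions agree. Passing the check only permits the EFA; it neither selects items nor declares validity.

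**The alpha rule would catch a weak instrument.** The Reliability analysis section requires Cronbach's α ≥ 0.70. Seven items correlated at 0.05 have α = 7 × 0.05 / (1 + 6 × 0.05) = 0.27 and would fail. This stands only in part. All 45 items at 0.05 have α = 45 × 0.05 / (1 + 44 × 0.05) = 2.25/3.2 = 0.70. Seven-item domains at 0.25 have α = 1.75/2.5 = 0.70, yet with near-independent domains their KMO is often below 0.7.

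**The CFI clause is an editing slip that no analyst would apply.** Agreed as to cause. The intended rule can be recovered, and a reader should not infer that a model with CFI near zero would be accepted. It is still the current text, and it leaves a declared criterion without a stated limit.

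**Stronger readings that the document does not support:**

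- *That principal components with a 0.4 loading limit is an error that keeps weak items.* It is a common, cited convention, used here with a single-factor condition, parallel analysis and a CFA in a separate subset. In population terms, an item with a true loading of 0.30 among items loading 0.5–0.7 has a component loading of 0.46–0.50 with four items per factor, 0.41–0.45 with five, 0.37–0.40 with seven and 0.34–0.36 with twelve. Whether it passes therefore depends on items per factor and on the other loadings. Table 1 lists 3 to 12 secondary indexes per dimension, 32 in all, but the questionnaire is expected to have 40–45 items and the factors are still to be found.
- *That the surviving items are the latent class indicators, so that any fault passes straight into the main analysis.* The Phase 4 section classifies people by six types of need, while the Delphi section speaks of making both scale and items binary. The unit of analysis is not settled by the text.
- *That the check is always met.* With truly uncorrelated items it passes only 5–7%.

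**Conclusion.** Wrong as written, on two thresholds.

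1. The *or* makes the KMO limit inoperative at the planned pilot size. At an average correlation of 0.05 the printed rule passes 99–100% and the joint rule 0%. The gap closes by 0.15, so the effect is confined to weak or borderline item sets. This rests on a 1:1 split, normal items and the simple correlation patterns shown.
2. The fit sentence assigns 0.08 to CFI, contradicts itself, and leaves RMSEA without a limit. This rests on the text alone.

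Both are defects of stated rules, not evidence that the questionnaire will prove invalid. The extraction method is not part of the error.

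**What to change.** - Require Bartlett p < 0.05 **and** KMO > 0.7 before the EFA.
- Restate the fit rule as CFI ≥ 0.90, RMSEA ≤ 0.08 and SRMR ≤ 0.08, each index with its own limit.

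Both are wording changes, with the same software and no extra participants. The cost is that the joint rule can stop an EFA that the printed rule would allow. In the six-domain example with correlations of 0 to 0.05 between domains, it would do so in 36–99% of samples (100% less the 1–64% that pass).

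Optional, and not a correction: principal-axis or maximum-likelihood extraction, keeping oblimin and parallel analysis, would match the common-factor model of the later CFA better than principal components. A few more items might then be dropped.
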